#### Physical activity

The level of physical activity in the participants will be assessed using the long form (27 items) of the International Physical Activity Questionnaires (IPAQ) that has been validated for the Iranian population [32]. IPAQ examines four domains of physical activity, including work (7 items), transportation (6 items), household (6 items), and leisure time activities (6 items) during the past 7 days. It also has two questions about sitting time.

#### Strategies to promote participant retention and complete follow-up

On the two test days, the researcher will be present at all stages of the study and measurements and will monitor the study process. Phone calls will be arranged to remind participants regarding the next test appointment.

#### Data management

In the current study, the database will be generated from IC, Sphygmocor XCEL, and laboratory assay results in the Excel software and SAS software version 9.4. To increase the accuracy of data collection, all data will be collected by principal investigators. Finally, data will be analyzed using the SAS software. For data security, usernames and passwords will be provided only to the study researchers.

#### Confidentiality

The data of the participants will be stored securely. A coded ID number will be considered to record the laboratory specimens, reports, and collected data. The collected data will remain confidential, and only the research team will have access to the collected data. For international prospective meta-analyses, the anonymized data will be made available to other researchers.

#### Plans for collection, laboratory evaluation, and storage of biological specimens for genetic or molecular analysis in this trial/future use

For future use, the remaining samples will be stored at − 80 °C at Mashhad University of Medical Sciences.

#### Statistical methods for primary and secondary outcomes

Data will be defined as means ± SDs for the normally distributed continuous variables and median and interquartile range for non-normally distributed continuous variables. Qualitative variables will be expressed as the distribution frequency in different categories (%). Two-sample independent *t* tests will be used to analyze comparisons between the conditions. Viscosity and palatability of the test meals will be analyzed using independent *t*-tests.

Statistical analyses will be performed using PROC GLIMMIX in SAS version 9.4. The carryover effect will be tested; the impact of time and protein source will be calculated if the carryover effect is significant; and if not, only the comparison will be done in parallel in the first period as a covariance analysis. The 2-factor repeated-measures design will be analyzed as generalized linear mixed models to assess the effect of time and protein source in various phases of the study.

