### Trial design

This is an acute randomized crossover clinical trial study of two protein-based breakfast meals with different protein sources (AP and PP). Each participant will consume two different test meals on different days with a 1-week washout period in between. Figure 1 shows the diagram of enrollment, intervention, and assessments.

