### Interventions

#### Explanation for the choice of comparators

In the present study, we aimed to compare two intervention conditions, including AP and PP conditions, and there is no control condition.

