### Assignment of interventions: allocation

#### Sequence generation

As the present study is a crossover study, all participants will receive both interventions. In the present study, only the intervention initiation meal will be randomized. Participants will be randomly allocated to AP or PP conditions based on a 1:1 ratio (simple randomization). The randomization will be performed using a random number table. A random sequence will be generated and sealed in envelopes by a person who is not a member of the research team. Each participant will randomly choose an envelope to be allocated to one of the two test meal conditions for the first trial. Then, the participants will receive the other test meal in the next trial after a 1-week washout period.

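### Independent t-tests are named for comparing the two meals although every man eats both, and the plan does not say whether they or the mixed model decide

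*Protocol article*

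**What the plan says.** Under *Trial design*, the protocol article states: "Each participant will consume two different test meals on different days with a 1-week washout period in between". *Sequence generation* repeats that "all participants will receive both interventions", so only the order of the meals is randomised. *Explanation for the choice of comparators* fixes what a condition is: "we aimed to compare two intervention conditions, including AP and PP conditions, and there is no control condition".

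*Statistical methods for primary and secondary outcomes* has two paragraphs. The first, after the descriptive statistics, says: "Two-sample independent *t* tests will be used to analyze comparisons between the conditions". It then adds: "Viscosity and palatability of the test meals will be analyzed using independent *t*-tests". The second names PROC GLIMMIX, gives a carryover rule, and says: "The 2-factor repeated-measures design will be analyzed as generalized linear mixed models to assess the effect of time and protein source".

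The t-test sentence is not restricted to baseline values, to the first period or to a supporting role. Neither paragraph says which analysis settles the comparison of the meals.

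**The concern.** The AP and PP values come in pairs from the same men, so they are not two independent samples. An independent t-test leaves the variation between men in the error term, and removing that variation is the main statistical reason for a crossover. If men who are high after one meal tend to be high after the other, the test overstates the standard error of the meal difference.

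The mixed model in the next paragraph can respect the pairing. But two analyses then address one contrast, with different standard errors and possibly different p-values, and no rule of precedence. The choice could be made after the results are seen. An interval that is too wide could also be misread as showing that the meals do not differ.

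**Working it through.** **Inputs.** From *Sample size*: REE difference 250 kcal/day, SD 330 kcal/day, average correlation 0.5, power 80%, 95% confidence, dropout 10%, 46 men. From *Trial design*: every man has both meals.

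**1. The plan's own figure.** m = 2 × (1.96 + 0.84)² × 330² × [1 + 4(1 − 0.5)] / (4 × 250²) = 2 × 7.84 × 108,900 × 3 / 250,000 = 20.49, rounded up to 21. Dropout: 20.49 / 0.9 = 22.8, rounded up to 23; × 2 = 46. The stated size reproduces. It counts 23 men per group, whereas all 46 men contribute both meals.

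**2. Standard error of the meal difference.** For N men, single-measurement SD sigma and between-meal correlation rho:

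- independent test: sigma × sqrt(2/N)
- paired: sigma × sqrt(2(1 − rho)/N)
- ratio: 1/sqrt(1 − rho)

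With N = 46, sigma = 330 and rho = 0.5, the independent test gives 330 × sqrt(2/46) = 68.8 kcal/day and the paired test 330 × sqrt(1/46) = 48.7. The 95% half-widths are about 1.96 × 68.8 = 135 and 1.96 × 48.7 = 95 kcal/day.

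**3. True type I error of the nominal 5% independent test.** Normal approximation: 2 × [1 − Phi(1.96 × ratio)].

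| rho | SE ratio | true alpha |
|---|---|---|
| 0.3 | 1.20 | 1.9% |
| 0.5 | 1.41 | 0.6% |
| 0.8 | 2.24 | 0.001% |

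A simulation of 40,000 trials with 41 men at rho 0.5 gave 0.65% for the independent test and 5.1% for the paired test.

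**4. Power with 41 completers** (46 × 0.9 = 41.4), sigma = 330. Only 250 kcal/day is the plan's effect; 150 and 100 are illustrative.

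| rho | difference (kcal/day) | independent | paired |
|---|---|---|---|
| 0.3 | 250 | 96% | 98% |
| 0.3 | 150 | 53% | 67% |
| 0.5 | 250 | 98% | 99.7% |
| 0.5 | 150 | 54% | 81% |
| 0.5 | 100 | 19% | 47% |
| 0.8 | 250 | 99.9% | >99.9% |
| 0.8 | 150 | 56% | 99% |

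**5. Sensitivity to the meaning of 330.** The text describes 330 as belonging to the difference, while the formula uses it as sigma. At rho 0.5 the SD of a within-man difference is 330 × sqrt(2 × 0.5) = 330, so both readings agree. They part at high correlation. If 330 is the SD of the difference and rho is 0.8, the single-measurement SD is 330/sqrt(0.4) = 522 and the independent SE is 522 × sqrt(2/41) = 115.2. The paired SE is 330/sqrt(41) = 51.5. Independent-test power at 250 kcal/day is then Phi((250 − 1.96 × 115.2)/51.5) = Phi(0.47) = 68%.

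**The case against.** The strongest reply is that the section already names a model suited to the design. PROC GLIMMIX and the repeated-measures model come straight after, and the t-test sentence sits among descriptive statements, so it could be meant as support. This stands in part: a reader might infer that the plan discards the pairing altogether, and the mixed model shows that it need not. But the text assigns no supporting role to the t-test and no deciding role to the model.

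The t-test might instead be meant for first-period data, where independent samples would be legitimate. The text does not support that, because it describes the first-period comparison as a covariance analysis.

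Three further objections stand and limit the point.

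- **Direction.** A reader might infer from a wrong standard error that false positives rise. With positive correlation they fall; the test is conservative.
- **Power.** A reader might infer that power drops from the nominal 80% to about 51% at rho 0.5, since 1 − Phi(1.96 × 1.414 − 2.80) = 0.51, or to about 6% at rho 0.8. Those figures hold only for an effect at which the paired test has exactly 80% power. On the plan's inputs the paired test has far more, because about 14 men would suffice: (1.96 + 0.84)² × 330² / 250² = 13.7.
- **Correlation.** The 0.5 under *Sample size* is an average correlation used with four repeated measures. It is not stated to be the correlation between meals, hence the range.

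Viscosity is also outside the point. It is measured on the meal with a viscometer, so an independent test can be right there.

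**Conclusion.** The point holds in a narrow, conservative form. A test that does not fit the crossover is named without restriction for the meal comparison, beside a model that can fit it, and precedence is left open.

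If the independent test were used, intervals would be about 41% too wide at rho 0.5 and the true type I error about 0.6%. These figures assume that 0.5 can stand for the between-meal correlation. The planned REE comparison would hardly suffer: power stays about 98% at rho 0.5. The exception is a high correlation combined with 330 read as the SD of the difference (68% at rho 0.8).

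The loss falls on smaller effects and on the other primary outcomes (appetite, DIT, SO, PWV and PWA), for which the article states no effect size. Smaller effects are plausible on the article's own account. Its *Background* cites a 2% difference in 24-hour energy expenditure between pork and soy, and 250 kcal/day would be 2% only of 250/0.02 = 12,500 kcal/day. That is a different measure from postprandial REE, so it indicates scale only.

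Palatability shares the fault if each man rates both meals, which the article implies but does not state.

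**What to change.** - Delete the independent t-test sentence for comparisons between the meals.
- Name the AP-PP contrast from the mixed model as the deciding test, with participant as a random effect and meal, period and sequence as fixed effects, alongside the time factor already planned.
- If a simple test is wanted as support, compare the within-participant differences between the two sequences, which adjusts for period.
- Split the viscosity and palatability sentence. Analyse palatability as paired where each man rates both meals, and leave the independent test for viscosity.

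The cost is a few sentences in the statistical section. Conduct, visits and sample size are unaffected, and *Trial status* says that enrolment had not begun when the protocol was written.

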### Sample size

The sample size was calculated concerning the primary outcomes observed in our previous study and considering desired power of 80% and 95% confidence interval. Considering the mean and standard deviation for the difference in REE of 250 and 330 kcal/day, respectively, an average correlation of 0.5, and a possible dropout rate of 10%, the sample size was calculated as 46 participants (23 participants in each group).$${\varvec{m}}=\frac{{2\left({{\varvec{z}}}_{1-\frac{\boldsymbol{\alpha }}{2}}+{{\varvec{z}}}_{1-{\varvec{\beta}}}\right)}^{2}\boldsymbol{ }{{\varvec{\sigma}}}^{2}[1+{\varvec{n}}(1-{\varvec{\rho}})]}{{{\varvec{n}}{\varvec{d}}}^{2}}\boldsymbol{ }=\boldsymbol{ }\frac{{2\left(1/96+0/84\right)}^{2}\times {330}^{2}\times [1+4(1-0.5)]}{4{(250)}^{2}}=21\simeq 23$$

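### The carryover rule is printed the wrong way round: no detected carryover drops visit 2, detected carryover keeps it, and the next sentence of the plan contradicts the rule

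*Protocol article*

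**What the plan says.** The Trial design section describes a two-period crossover: "Each participant will consume two different test meals on different days with a 1-week washout period in between". Under Sequence generation, only the order of the two meals is randomised.

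Statistical methods for primary and secondary outcomes then says that carryover will be tested and sets two branches:

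- **Carryover significant, with the turn to the alternative:** "the impact of time and protein source will be calculated if the carryover effect is significant; and if not".
- **Carryover not significant, where the alternative reads:** "only the comparison will be done in parallel in the first period as a covariance analysis".

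The section closes with a sentence that carries no condition: "The 2-factor repeated-measures design will be analyzed as generalized linear mixed models to assess the effect of time and protein source in various phases".

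The article gives neither the level of the carryover test nor the way it is computed. No other section restates or corrects the rule.

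**The concern.** Carryover contaminates the second visit. Falling back on the first period therefore makes sense only when carryover has been found. The printed rule does the opposite.

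Two things are at stake:

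- **No carryover**, which is what the washout is meant to secure. The rule throws away the second visit and with it each man's comparison with himself, which is the reason for a crossover.
- **Carryover present.** The more clearly the test shows it, the more likely the contaminated visit is to enter the estimate.

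The rule stands under the heading for all primary and secondary outcomes, so it is not confined to one endpoint. Because it conflicts with the sentence after it, an analyst would have to choose between two instructions, possibly after seeing data.

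**Working it through.** **Inputs.** The Sample size section gives an REE difference of 250 and an SD of 330 kcal/day, correlation 0.5, 10% dropout, 46 men (23 per group), and 80% power with 1.96 and 0.84 in the formula. Assumptions not in the article: the 0.5 also holds between visits; 330 is the SD within a condition (read instead as the SD of the paired difference, it gives the same crossover standard error at correlation 0.5); completers = 46 × 0.9 ≈ 41; the covariate of the covariance analysis is the visit-1 fasting value, also correlated 0.5 with the outcome.

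**1. The plan's own figure.** 2 × (1.96 + 0.84)² × 330² × [1 + 4(1 − 0.5)] / (4 × 250²) = 20.49, so 21. Then 21 × 1.1 = 23.1, taken as 23 per group. The figure reproduces. It comes from a two-group repeated-measures formula, which matters in step 4.

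**2. How often visit 2 is dropped.** With no true carryover, a test at level α is non-significant with probability 1 − α: 95% at 5%, 90% at 10%.

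**3. Information lost** (N men, SD σ, correlation ρ).

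- Both visits: variance 2σ²(1 − ρ)/N
- First period, unadjusted: 4σ²/N; ratio 2/(1 − ρ) = 4 at ρ = 0.5
- First period with covariate: 4σ²(1 − ρ²)/N; ratio 2(1 + ρ) = 3 at ρ = 0.5

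The first period alone keeps 1/4 or 1/3 of the information, a loss of 75% or 67%.

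**4. Power at 250 kcal/day** (noncentral t, two-sided 5%, ρ = 0.5).

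| | 41 completers: SE | Power | 46 men: SE | Power |
|---|---|---|---|---|
| Both visits | 51.5 | 99.7% | 48.7 | 99.9% |
| First period, unadjusted | 103.1 | 66% | 97.3 | 71% |
| First period, covariate | 89.3 | 78% | 84.3 | 83% |

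First-period power stays near the target because 23 per group was sized for a two-group comparison. That cushion exists only at 250 kcal/day. For an illustrative 148 kcal/day, which both visits detect with 80% power in 41 men, the first period gives 29% (unadjusted) or 37% (covariate).

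**5. When carryover is present.** Let λ be the AP carryover minus the PP carryover into visit 2. The both-visit estimate has expectation (true difference) − λ/2. With no true meal difference and λ = 250, the bias has size 125 kcal/day. In simulation (46 men) the both-visit test then rejects in 71% of trials and the first-period test in 5%. The carryover test itself, at the 5% level, is significant in only about 30%.

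**6. Swapping the branches.** Simulated type I error with no carryover and no meal effect, pre-test at 5% or 10%:

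- unadjusted first-period test: about 7–9%;
- covariance analysis: about 5–7%, and close to 5% if carryover is tested on the change in fasting values between visits.

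The rule as printed does not inflate type I error when there is no carryover; it gives about 1–4%.

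**The case against.** The best defence is that this is a slip of wording, probably a lost negative, in a condensed article, and that the closing sentence shows a mixed model was meant all along. The slip is plausible. But the printed text is an explicit instruction for both outcomes of the test, nothing elsewhere corrects it, and the closing sentence adds a conflict without withdrawing the rule. What does stand is that one cannot say which analysis would actually be run.

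It is also fair that the use of both visits in the significant branch is inferred. The inference rests on the shared reference to time and protein source in the mixed-model sentence and on the contrast with a first-period-only comparison. No other reading fits well.

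Two stronger readings are tempting and are not supported:

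- **That the trial loses most of its power.** On the protocol's own REE inputs it loses most of its information but keeps 66–83% power. Figures such as 29% need an effect well below 250 kcal/day, which the article does not state.
- **That the plan has a type I error of 7–9%.** That belongs to a rule with the branches swapped and an unadjusted first-period test. The plan names a covariance analysis, for which the excess is smaller, and the rule as printed shows none in the absence of carryover.

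**Conclusion.** The point holds: the two branches are reversed, and they contradict the unconditional mixed-model sentence that follows. Read literally, with no true carryover, visit 2 would be dropped in about 90–95% of analyses, at a cost of two thirds to three quarters of the information. For REE at the planned effect, power falls from above 99% to about 66–78% (41 completers) or 71–83% (46 men).

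The loss is larger for smaller effects. Appetite, DIT, SO, PWV and PWA are also primary and have no stated effect sizes, so the REE margin does not cover them. Where carryover exists and is detected, the estimate used would be the biased one.

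These sizes rest on a between-visit correlation of 0.5 and, for the upper power figures, on a fasting covariate correlated 0.5 with the outcome. The reversal and the contradiction rest on the text alone. This should be corrected before enrolment.

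**What to change.** Delete the carryover-dependent branch. State that the primary analysis always uses both visits in one mixed model with protein source, time, their interaction, period and sequence as fixed effects and participant as a random effect.

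Justify the absence of carryover by the 1-week washout. Report visit-2 fasting values by sequence as a descriptive check. Optionally report the first-period comparison as a sensitivity analysis. Neither should affect the choice of primary analysis.

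Swapping the two branches would restore the usual direction but keep a weak pre-test in charge of the analysis, so it is second best.

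The cost is rewording two sentences. No extra participants or measurements are needed, and the Trial status section says enrolment has not begun.

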**Fig. 1 Fig1:**
[figure not shown]
Study diagram of enrollment, interventions, and assessments

Participants will be instructed not to drink alcohol or engage in severe physical activity within 48 h before each test day. Participants will not be allowed to fast the day before the test days. On the morning of the test day, participants will travel to the research center at Imam Reza Hospital by taxi (with a minimum activity) to arrive at 7 a.m. Participants should abstain from food, drinks (except water), alcohol, and caffeine for 12 h.

On arrival, anthropometric parameters will be measured, and an intravenous catheter will be inserted into an antecubital arm vein. Before consuming the test meals, fasting measurements of indirect calorimetry (IC), PWV and PWA, and subjective appetite will be performed, and venous blood will be collected via the intravenous catheter. Then, participants will be given 15 min to eat the test meals under the researcher’s supervision until the test meal is wholly consumed.

Afterward, postprandial phase tests, including IC, PWA, PWV, and assessing the appetite response, will be performed. Blood samples will also be collected within 6 h. All the tests will be performed in the same conditions (e.g., quiet and temperature-regulated room).

Figure 2 depicts the schedule of the study days. Time points were determined according to the preliminary results of our previous study. The testing conditions will be repeated on the next test day.

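### The main mixed model names only time and protein source: it has no period term and no adjustment for each day's fasting value, while simple randomisation leaves the two meal orders free to be unequal

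*Protocol article*

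**What the plan says.** The section on statistical methods for primary and secondary outcomes gives the main model as: "The 2-factor repeated-measures design will be analyzed as generalized linear mixed models to assess the effect of time and protein source". Carryover is handled by a separate preliminary test: "The carryover effect will be tested; the impact of time and protein source will be calculated if the carryover effect is significant". In the other case, "only the comparison will be done in parallel in the first period as a covariance analysis". That is the section's only mention of covariance adjustment, and it names no covariate.

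The design has two visits: "Each participant will consume two different test meals on different days with a 1-week washout period in between". Fasting readings are taken on each test day: "Before consuming the test meals, fasting measurements of indirect calorimetry (IC), PWV and PWA, and subjective appetite will be performed". Fasting blood is drawn as well.

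Under Sequence generation, "Participants will be randomly allocated to AP or PP conditions based on a 1:1 ratio (simple randomization", and "The randomization will be performed using a random number table". No blocking is mentioned. The Sample size section counts on equal groups: "the sample size was calculated as 46 participants (23 participants in each group".

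**The concern.** In a two-period crossover each man supplies one AP-PP difference. That difference contains the meal effect plus or minus any difference between first and second visit, with the sign set by his meal order. If the orders are equally frequent, the visit difference cancels from the mean but stays in the spread of the differences. If they are unequal, part of it stays in the mean as well. A period term removes both effects.

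A visit difference is plausible on the protocol's own terms. Each test day involves cannulation, mask calorimetry and tonometry, and the Indirect calorimetry section says that stress harms calorimetry quality. 'Time' most naturally means the repeated readings within a day, because the same section uses the word period for the visit. If 'time' meant visit instead, the repeated readings would be unmodelled.

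The fasting value raises a related question. It is measured on both days, but the main model does not say whether it is a covariate, a level of the time factor, or unused.

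**Working it through.** **Inputs from the protocol.** N = 46, as 23 per group; difference 250 kcal/d; SD 330 kcal/d; correlation 0.5; z values 1.96 and 0.84; dropout 10% (Sample size). Simple 1:1 allocation (Sequence generation).

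**The plan's own figure.** m = 2 x (1.96 + 0.84)^2 x 330^2 x [1 + 4(1 - 0.5)] / (4 x 250^2) = 20.49, rounded up to 21. Allowing for dropout, 20.49/0.9 = 22.8, so 23 per group and 46 in all. The stated figure reproduces.

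**Balance of the two orders.** Under Binomial(46, 0.5):

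| Split | Probability | Share of a period effect absorbed, \|n1-n2\|/46 |
|---|---|---|
| exactly 23:23 | 11.7% | 0 |
| 26:20 or worse | 46.1% | at least 13.0% |
| 28:18 or worse | 18.4% | at least 21.7% |
| 30:16 or worse | 5.4% | at least 30.4% |

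The expected gap is 5.38 men, so the average share absorbed is 5.38/46 = 11.7%. With 42 men (twice the formula's 21), an exact split has probability 12.2%, and 26:16 or worse 16.4%, absorbing at least 10/42 = 23.8%.

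**Assumptions.** The protocol gives no period effect, so a range is used: pi = 50, 100, 165 and 250 kcal/d between visits. The SD of the within-person AP-PP difference is taken as 330.

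**Formulas.**
- Bias without a period term = pi x (n1 - n2)/N.
- Model SE without a period term = sqrt{[330^2 + pi^2 x 4 n1 n2/N^2]/N}.
- SE with a period term = (330/2) x sqrt(1/n1 + 1/n2), which is 48.7 at 23:23 and 49.8 at 28:18.
- Type I error uses the t critical value on 45 df times the model SE. The true SE of the mean difference is 330/sqrt(46) = 48.7, and the estimate is shifted by the bias.

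Example at pi = 100 and 28:18: bias = 100 x 10/46 = 21.7. At 23:23: SE = sqrt[(330^2 + 100^2)/46] = 50.8.

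**Results without a period term.**

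| pi (kcal/d) | Bias at 28:18 | Type I error at 28:18 | SE at 23:23 (48.7 with period) | Type I error at 23:23 |
|---|---|---|---|---|
| 50 | 10.9 | 4.7% | 49.2 | 4.2% |
| 100 | 21.7 | 5.5% | 50.8 | 3.5% |
| 165 | 35.9 | 6.8% | 54.4 | 2.4% |
| 250 | 54.3 | 8.3% | 61.0 | 1.2% |

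Type I error below 5% in the last column means that the test is conservative and power is lost.

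**Fasting value.** The gain from adjustment cannot be computed, because the protocol gives no correlation between fasting and post-meal readings.

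**The case against.** The strongest reply is that this is a condensed article. The sentence may say which effects are of interest without listing every term, and covariates are often left to an analysis plan. This has some force, and the remedy may be no more than writing down what is already intended. But the text names a two-factor model and places covariance adjustment only in the first-period comparison, so as written neither term is in the main model.

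Second, visit effects are partly controlled. Conditions are repeated on the second day, rest is required before calorimetry, testing is postponed for a stressed participant, and Table 1 ticks calorimetry and velocimetry at time points before visit 1. These steps may make a period effect small. They do not show that it is absent.

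Third, a reader might infer that simple randomisation is itself a flaw. It is not: it is valid, and over repeated allocations the estimate is unbiased. The bias above is conditional on the split actually drawn. Once period is modelled, 28:18 instead of 23:23 raises the SE only from 48.7 to 49.8, so blocking is a refinement.

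Fourth, a reader might rank the missing sequence term with the missing period term. In a 2x2 crossover, sequence is aliased with carryover, which is tested separately, and leaving it out does not bias the within-person contrast.

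Fifth, a reader might infer that the meal effect is diluted to 75%, since fasting would be one of four calorimetry times (0, 60, 180 and 300 min). That holds only if fasting is coded as a time level and the effect is read from the protein-source main effect. The protocol states neither. The same coding would give 4/5 = 80% for PWV and blood, which have five times each.

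**Conclusion.** The point holds for the period term and the fasting value. As stated, the main model includes neither, and the randomisation does not assure the balance that would keep a period effect out of the estimate.

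The size depends on a period effect that the documents do not give. At 28:18 an assumed 100 kcal/d yields a bias of about 22 kcal/d, or 22/250 = 9% of the trial's own design difference, and type I error of about 5.5%. At the average imbalance the bias is about 12 kcal/d (100 x 11.7%), or 5%. Only effects towards 250 kcal/d do marked damage. All of this also rests on 330 being the SD of the within-person difference.

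A reader might compare the 22 kcal/d with the 2% difference in 24-h energy expenditure cited in the Background and call it large. That needs a daily base in kcal that the protocol does not state, so the comparison is not used here.

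The change is worth making because it is specific and nearly free. The omission does not make the trial invalid.

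**What to change.** State one model for the analysis that uses both visits:

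- outcome: the post-meal readings;
- fixed effects: meal, post-meal time, meal x time, period, and that day's fasting value;
- random participant effect, with correlation among readings within a day.

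If the fasting reading is kept as a level of time instead, say that the meal effect is read from post-meal contrasts relative to fasting, not from the protein-source main effect.

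A sequence term is optional. So are permuted blocks of varying size, which would keep the orders near 23:23 at allocation. The period term is still needed with blocking, because dropout, exclusions after recruitment and the per-protocol analysis can unbalance the orders later.

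The cost is one model statement and one or two degrees of freedom, with no change to N. The Trial status section says that enrolment had not begun, so both the model and, if wanted, the list could be settled beforehand.
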